### **2.2. Endpoints**

- 3.2.1 Determine the frequency of laboratory confirmed SARS-CoV-2 cases, defined by RT-PCR positivity within 28 days observational period, in high risk population with routine COVID-19 positive contacts.
- 3.2.2 Evaluation of the safety of aerosol combination therapy as the pre-exposure prophylaxis for COVID-19.

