### **2.3. Design**

The study is intended as a low-interventional prospective open-label clinical study of aerosol combination therapy in a cohort of healthy adult volunteers regularly exposed to COVID-19 positive contacts.

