### **2.4. Population**

This is an open-label study is intended to obtain preliminary estimates in healthy adults of the efficacy and safety of the combination medication. Based on the observational trials in high risk individuals exposed to routine COVID-19 positive contacts frequency of SARS-CoV infection confirmed by RT-PCR is 11.1% (García I.S. et al., 2020). We expect that the investigated pre-exposure prophylaxis allows to eliminate SARS-CoV-2 positive cases to 3% or less during observational period. With Alpha error rate of 0.05, beta error 0.85, we need to include 96 subjects.

Rare adverse events (AEs) are not demonstrable in a clinical study of this size. With the assumption that all enrolled subjects will likely complete the treatment and safety visits in this relatively short duration study, the following statistical considerations apply. With 100 subjects in the treatment group, the chance of observing at least one AE of probability 5% or more is approximately 95%. Therefore, if no AEs of a given type occur, we can be relatively confident that they will occur in fewer than 5% of people.

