### **2.6. Exclusion Criteria**

Healthy volunteers cannot be included in the trial if they meet at least one of the following criteria.

2.6.1. Criteria related to the disease:

Detection of SARS-CoV-2 virus RNA by polymerase chain reaction (PCR) in biomaterial samples and/or positive enzyme-linked immunosorbent assay ELISA IgM and ELISA IgG to the virus in a healthy volunteer;

2.6.2. Criteria related to the combination medication, previous therapy and concomitant therapy:

Hypersensitivity or individual intolerance to the components of the combination therapy according to the medical history.

2.6.3. Criteria related to the concomitant pathology:

According to the medical history and physical examination:

- any diseases or conditions that, in opinion of the investigator, would make it difficult to interpret the results of treatment or may limit the participation of a healthy volunteer in the study.

According to screening laboratory tests:

- related to the compliance of healthy volunteers in the study;
- any diseases or conditions that, in opinion of the investigator, would make it difficult to interpret the results of treatment or may limit the participation of healthy volunteers in the study;

Healthy volunteers who, in the opinion of the investigator, are obviously or likely unable to understand and evaluate the information regarding this study within the process of signing the informed consent form, in particular regarding the expected risks and possible discomfort.

The inability or unwillingness of a healthy volunteer to follow the rules for carrying out the study and participating in a clinical trial.

2.7. **Early Discontinuation Criteria**

2.7.1. A healthy volunteer will be excluded from the study if SARS-CoV-2 virus RNA is detected in biomaterial samples by a polymerase chain reaction (PCR) for COVID-19 or if enzyme-linked immunosorbent assay (ELISA) IgM and ELISA IgG results are positive.

2.7.2. A healthy volunteer may withdraw their consent to participate in the study at any time and without giving reasons. The investigator may also decide on early discontinuation of the participation of a healthy volunteer in the study at any time if the patient's condition requires it.

2.7.3. Main reasons for early discontinuation of participation of a healthy volunteer in the study:

Individual intolerance to the combination medication or any of its components;

Failure to meet the inclusion and exclusion criteria;

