Refusal of a healthy volunteer to participate in the study or the withdrawal of informed consent by a healthy volunteer;

Development of adverse events that prevent further prophylactic therapy with the medication;

The emergence of a serious adverse event in a healthy volunteer;

The emergence of exclusion criteria in the course of the study;

Any condition of a healthy volunteer that requires, in the opinion of the investigator, the withdrawal of the patient from the study;

Discontinuation of the trial by the research center, investigator, or regulatory authority.

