## 6. STATISTICAL ANALYSIS

The methods for statistical analysis of the obtained data are determined by the nature, type, and distribution of the data. The applicability of a number of statistical methods will be evaluated upon the completion of the data collection due to the unknown distribution, sample uniformity, etc. In the course of the analysis, the list of methods used can be expanded if necessary for high-quality data processing.

Statistical processing of data obtained in the study will be carried out using statistical programs or other special software that would ensure high quality of the results. Interval (quantitative) data will be described using the arithmetic mean, standard deviation, median, lower (25%) and upper (75%) quartiles, minimum and maximum values. Categorical (qualitative) data will be described using absolute and relative frequencies. To compare normally distributed quantitative data, standard parametric criteria shall be employed: Student's t-test for dependent/independent samples and analysis of variance (ANOVA) for repeated measurements. For the comparison of quantitative data that are not normally distributed, standard nonparametric tests shall be employed. The frequencies of the variables will be compared between the groups using Pearson's  $\chi^2$  test or Fisher's exact test.

AEs will be analyzed based on the frequency of adverse events/serious adverse events. Adverse events registered within the study will be presented by incidence rate (the number of patients with AEs and the number of such AEs in the group). AEs will also be presented by their intensity and relationship with the administration of the combined medicinal product.

Regardless of the reason for the termination of the study, the data of all enrolled healthy volunteers will be taken into account when analyzing the efficiency and safety of the investigational therapy.

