## 8. APPENDICES

### Appendix 1

|                                                                   | Study Plan |           |           |   |    |           |
|-------------------------------------------------------------------|------------|-----------|-----------|---|----|-----------|
|                                                                   | Procedures | Screening | Treatment |   |    | Follow-up |
|                                                                   | Visit      | 0         | 1         | 2 | 3  | 3 4       |
|                                                                   | Days       | -2 - 0    | 1         | 7 | 14 | 21±1 28±1 |
| Informed Consent                                                  |            | X         | -         | - | -  | -         |
| Insurance                                                         |            | X         |           |   |    |           |
| PCR for SARS-CoV-2 RNA                                            |            | X         | X         | X | X  | X         |
| ELISA IgM and IgG to SARS-CoV-2                                   |            | X         | -         | - | -  | X         |
| Demographics, Complaints and Medical History, Anthropometric Data |            | X         | X         | - | -  | -         |
| Inclusion and Exclusion Criteria Assessment                       |            | X         | X         | X | X  | X         |
| Physical Examination                                              |            | X         | X         | X | X  | X         |
| Vital Signs Assessment (BP, HR, RR, TEMP)                         |            | -         | X         | X | X  | X         |
| Exclusion Criteria Assessment                                     |            | X         | -         | - | -  | -         |
| Previous Therapy Assessment                                       |            | X         | X         | X | X  | X         |
| Concomitant Therapy Assessment                                    |            | X         | X         | X | X  | X         |

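### Section 2.7.3 lets entry criteria end study participation after dosing has begun, with no PCR afterwards, so 28-day infection status can go unascertained

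*Protocol*

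**What the plan says.** The primary endpoint in Protocol section 2.2 is laboratory-confirmed infection, "defined by RT-PCR positivity within 28 days observational period". Section 2.3 describes a "low-interventional prospective open-label clinical study of aerosol combination therapy in a cohort of healthy adult volunteers", so there is no concurrent control. The comparison is with the external figure in section 2.4 ("frequency of SARS-CoV infection confirmed by RT-PCR is 11.1" per cent).

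Section 2.7.3 gives the main reasons for early discontinuation of participation in the study. Two of them refer back to eligibility: failing the inclusion and exclusion criteria, and "The emergence of exclusion criteria in the course of the study". The criteria imported in this way from section 2.6.3 include:

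- "The inability or unwillingness of a healthy volunteer to follow the rules for carrying out the study and participating in a clinical trial";
- any disease or condition that, in the investigator's opinion, "would make it difficult to interpret the results of treatment or may limit the participation of a healthy volunteer in the study".

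The row "Inclusion and Exclusion Criteria Assessment" in the Appendix 1 Study Plan is marked from screening through follow-up. The record forms for Visits 1 to 4 repeat both 2.7.3 items as yes/no questions. Appendix 1 marks PCR at the scheduled visits, and no section provides for PCR or status follow-up after a volunteer has left. Section 6 says that "the data of all enrolled healthy volunteers will be taken into account", whatever the reason for termination.

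**The concern.** An entry criterion protects the sample before dosing. Once it is used after the first dose to end participation, it decides whose endpoint is observed. Someone with symptoms and a negative Day 7 PCR, or someone who has stopped following the study rules, may be taken out with up to three weeks of the 28-day window still to run. Section 1.2 gives an incubation period of 2 to 14 days, so a negative test at removal does not settle the outcome.

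The study is open-label with one cohort, so no control arm loses cases in the same way. Infections missed after removal can only lower the observed rate if the volunteers concerned are treated as uninfected, and a lower rate is what would be read as efficacy against 11.1%. An analysis plan cannot repair this, because the PCR results would never have been collected.

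**Working it through.** **1. The route through the text.** Section 2.7.3 ends participation. The criteria come from 2.6.3. Appendix 1 and the Visit 1 to 4 forms prompt the check. PCR is tied to scheduled visits, which end with participation. Section 6 keeps data already collected but does not say how a missing 28-day status is counted.

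**2. Conflicting rows.** Appendix 1 has a row for the combined inclusion and exclusion assessment, marked through follow-up, and a separate row for exclusion criteria alone, marked at screening only. The forms print the full entry list at Visits 0 and 1, and at Visits 1 to 4 a discontinuation list headed as an assessment of exclusion criteria. Schedule and forms do not agree on which assessment belongs to which visit.

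**3. The plan's own sample size (section 2.4).** Inputs: p0 = 0.111, p1 = 0.03, alpha 0.05 taken as two-sided, and the stated beta error of 0.85 read as power 0.85.

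n = [(z_α√(p0q0) + z_power√(p1q1)) / (p0 − p1)]²
= [(1.960 × 0.3141 + 1.036 × 0.1706) / 0.081]² ≈ 95.7, rounded up to 96.

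The figure reproduces and contains no allowance for early removal.

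**4. Hypothetical effect of unseen infections.** The 96 is the protocol's. The rest is assumed: an inert product with true risk 11.1%, an exact success rule, and removed volunteers counted as non-cases. Four or fewer cases is the largest count whose exact lower tail at 11.1% stays within 0.025. Expected infections: 96 × 0.111 ≈ 10.7. If a fraction m goes unseen, the apparent risk is 0.111 × (1 − m), and false success is P(X ≤ 4) for a binomial with n = 96.

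| m | Apparent risk | False success, ≤4 cases | False success, ≤5 cases |
|---|---|---|---|
| 0 | 11.1% | 1.5% | 3.8% |
| 20% (about 2 infections) | 8.9% | 6.4% | 13.6% |
| 30% (about 3 infections) | 7.8% | 12.5% | 23.5% |

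The result turns on few people. An observed 3/96 has an exact one-sided p of 0.0045 against 11.1%. With three unseen cases added, 6/96 gives 0.081.

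**5. How much removal this would take.** Assume infections spread evenly over 28 days and removal at Day 7 after that day's PCR. Each removal then hides at most 21/28 = 75% of that volunteer's risk.

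- Removal unrelated to risk: hiding 20% needs 0.20/0.75 ≈ 27% of the cohort removed; hiding 30% needs 0.30/0.75 = 40%.
- Removed volunteers at three times the risk of the others: solve 0.75 × 3f/(1 + 2f) = m. For m = 20%, f ≈ 11%, about 10 of 96. For m = 30%, f ≈ 18%, about 17 of 96.

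**The case against.** The strongest reply is that the text allows removal but does not order it. Section 2.7.3 lists main reasons, whereas 2.7.1 (positive PCR or serology) says the volunteer will be excluded. Section 2.4 expects nearly everyone to complete. A volunteer assessed at a visit has a PCR scheduled at that visit, so only later infections are lost. Step 5 shows that hiding even 20% of infections would take substantial removal in a healthy cohort. All of this stands, and it is why the frequency must be called unknown.

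Three stronger readings are tempting and are not supported.

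- A reader might infer that anyone who misses doses or feels unwell must leave. The protocol does not say so, and a single missed inhalation is not plainly unwillingness to follow the rules. Nor are both criteria a matter of opinion: only the disease-or-condition item carries the investigator-opinion wording.
- A reader might infer from section 6 that removed volunteers are counted as uninfected. Section 6 says only that their data are taken into account. The counting rule may lie in an analysis plan that is not shown.
- A reader might argue that non-adherent volunteers are at higher risk even if the product is inert. That would need a link between adherence and exposure, and none is documented. The symptomatic, PCR-negative volunteer is the clearer case.

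It might also be said that the forms confine entry criteria to Visits 0 and 1. The full list is printed only there, but the two items that re-apply it stand on the forms for Visits 1 to 4. What survives the reply is the ascertainment gap: participation can end on these grounds, and no later PCR is provided.

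**Conclusion.** The point holds as a gap in endpoint ascertainment. It does not show a measured bias. The protocol permits removal of PCR-negative volunteers on entry criteria after the first dose, and their 28-day status is then not collected. If they are counted as non-cases, the error runs toward a lower infection rate against 11.1%. The size cannot be stated from the protocol. The figures of 6.4% and 12.5% against 1.5% are illustrations that rest on an inert product, a cut-off of four cases, non-case counting, and 20% or 30% of infections unseen; the protocol states none of these. Removal on a positive PCR under 2.7.1 is the endpoint itself and is no part of the concern. The change is worth making because it is cheap and the lost data could not be recovered later.

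**What to change.** - State that sections 2.5 and 2.6 apply as eligibility criteria only up to the first dose.
- State in 2.7 that a volunteer without a positive PCR who stops the medication, or meets an entry criterion after the first dose, stays in the already-scheduled PCR visits to Day 28 unless consent is withdrawn. Say expressly that this includes 2.7.2 and the separate investigator-opinion ground in 2.7.3; otherwise the same volunteers can leave follow-up by that route. Say also how the sentence sits with the serology ground in 2.7.1.
- Leave decisions on treatment with the investigator.
- Amend the two eligibility-based items in 2.7.3 and in the Visit 1 to 4 record forms to match.
- Reconcile the two Appendix 1 rows with each other and with the forms.

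The cost is a wording amendment to 2.7, Appendix 1 and four form pages, plus a few scheduled PCR visits kept for volunteers who would otherwise have left. The planned 96 need not change. Keeping 96 evaluable by over-enrolling instead would take 96/0.95, 96/0.90 or 96/0.80, that is 102, 107 or 120 volunteers at an assumed 5%, 10% or 20% removal, and would not cure selective loss.

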## 2.8. **Duration**

The trial comprises the following stages:

The screening period lasts up to 2 days.

The treatment period lasts 14 days.

The follow-up period lasts 14 days.

The duration of the study for healthy volunteers will not exceed 30 days.

All visits can only take place in a specialized hospital.

## DESCRIPTION OF THE COMBINATION MEDICATION

**INN:** POTASSIUM CHLORIDE

**Brand names of the pharmaceuticals:** various

**Therapeutic classification:** therapeutic drug for electrolyte balance

**ATC code:** B05XA01 Potassium Chloride

**Composition and pharmaceutical form:**

Concentrate for solution for infusion, a clear, colorless or slightly yellowish liquid in ampules of 10 ml, 10 ampules in a package.

One milliliter of the solution contains the following:

Active substance: potassium chloride – 40 mg

Excipients: Dextrose monohydrate - 334 mg, hydrochloric acid solution 1 M - up to pH 3.0-4.0, DI water - up to 1 ml.

**Pharmacokinetics**

After intake, the drug is easily and passively absorbed (70%) in virtually any amount because its concentration (both from food and released by pharmaceuticals) is higher in the lumen of the small intestine than in the blood. In the ileum and colon, potassium is excreted into the intestinal lumen following the principle of conjugated exchange with sodium and excreted with bile (10%).  $T_{1/2}$  in the absorption phase is 1.31 hours.

**Pharmacological effect**

Potassium deficiency replenishing agent. Helps in maintaining the necessary intra- and extracellular levels of potassium. Potassium is the main intracellular ion and has an important role in the regulation of various body functions. It participates in maintaining intracellular osmotic pressure, nerve impulse conduction and transmission to innervated organs, contraction of skeletal muscles, and a number of biochemical processes. Reducing the excitability and conductivity of the myocardium at high doses suppresses automatism.

**Indications for the use of drug**

Hypokalemia of various origins, including vomiting, diarrhea, hyperaldosteronism, polyuria in chronic renal failure, and the use of certain drugs; arrhythmias, including glycoside intoxication; hypokalemic form of paroxysmal myoplegia.

**Contraindications:** impaired renal function, complete heart block.

**Side effects:** nausea, vomiting, diarrhea.

**Registered administration and dose:** iv infusion at a rate of 20-30 drops per minute.

**There are no data on the inhaled administration of the drug.**

**Manufacturers - owners of the registration license:**

GROTEX OOO (Russia), SINTEZ OAO (Russia), BINNOFARM AO (Russia) and others.

VIDAL 22.04.2020 [https://www.vidal.ru/drugs/potassium\\_chloride\\_\\_44667](https://www.vidal.ru/drugs/potassium_chloride__44667)

**INN:** INOSINE GLYCYL-CYSTEINYL- GLUTAMATE DISODIUM

**Brand names of pharmaceuticals:** Molixan®

**Therapeutic classification:** metabolic agent

**ATC code:** V03AX Other therapeutic products

**Composition and pharmaceutical form:** solution for intravenous and intramuscular administration; 1 ml of a 3% solution for injections contains inosine glycyL-cysteinyL-disodium glutamate - 30 mg; in ampules of 1 and 2 ml with a break ring or dot; 5 or 10 ampules in a blister pack, 1 blister in a cardboard box.

One milliliter of the solution contains the following:

Active substance: inosine glycyL-cysteinyL-disodium glutamate 30 mg.

Excipients: sodium acetate trihydrate 13.6 mg, diluted acetic acid up to pH 6.0, and water for injections up to 1 ml.

**Pharmacological effect:** antiviral, immunomodulatory, hepatoprotective.

**Mechanism of action:** regulates the thiol-disulfide exchange of epithelial and immunocompetent cells, the production of cytokines by macrophages, including interleukin-2,  $\alpha$ - and  $\gamma$ -interferons, inhibits the cytolysis of functionally active cells and induces apoptosis of virus-infected cells.

**Contraindications:** individual hypersensitivity, pregnancy, breastfeeding.

**Side effects:** uncommon - increased body temperature (up to 37.1–37.5°C), slight soreness at the injection site.

**Registered administration and dose:** iv, i/m for lasting and severe forms of acute viral hepatitis B: 10–30 mg/day daily, single-dose, duration of the course: 24 days (in combination with symptomatic and detoxification therapy). In the case of chronic viral hepatitis B: 10–30 mg/day, daily, single-dose, for 3 months or more (combination with antiviral chemotherapy is possible). In the case of chronic viral hepatitis C: 30–60 mg/day in 1-2 doses, treatment duration 3-6 months (in combination with antiviral chemotherapy).

**There are no data on the inhaled administration of the drug.**

**Owner of the registration license:** ZAO PharmaVAM (Russia)

**Manufacturers:** State Research Institute of Highly Pure Biopreparations of the Federal Medical-Biomedical Agency, Russian Cardiology Research and Production Complex of the Ministry of Health of Russian Federation

VIDAL 22.04.2020 [https://www.vidal.ru/drugs/molixan\\_\\_30093](https://www.vidal.ru/drugs/molixan__30093)

### **3. DOSAGE AND ADMINISTRATION OF A COMBINATION MEDICATION**

The combination medication is administered daily in the daytime 4 (four) times a day with an interval of at least 4 hours.

The combination of the medication is prepared per daily inhalation dose by mixing the following medication in the indicated amount *ex tempore*: 3% solution of inosine glycyl-cysteinyldisodium glutamate 4.0 ml and 4% potassium chloride solution 1.0 ml.

The combination medication should be used within 24 hours after preparation.

One milliliter of a solution of a combination medication contains active substances:

Potassium chloride 8.0 mg

Inosine glycyl-cysteinyldisodium glutamate 24.0 mg

A single inhalation dose of the combination medication is 1.25 ml.

The combination medication for inhalation is administered using a nebulizer equipped with a mouthpiece. The nebulizer is connected to the compressor to create the required air flow (5-8 L/min), and the nebulizer must be filled with at least 4 ml of the medicinal product.

The combination medication should be inhaled through the mouthpiece of the nebulizer in a calm and regular manner.

The nebulizer should be regularly cleaned following the manufacturer's instructions. Clean the cup of the nebulizer after each use. Wash the cup of the nebulizer and mouthpiece or mask with warm water and mild detergent (follow the manufacturer's instructions). The nebulizer should be thoroughly rinsed and dried by connecting the cup to the compressor or air inlet valve.

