## **Instruction for Use of Combination Medication**

### **1. Preparation of Combination Medication**

A combination of the medication is prepared per daily inhalation dose by mixing the following medication in the indicated amount *ex tempore*:

3% solution of inosine glycyl-cysteinyl-disodium glutamate - 4.0 ml;

4% potassium chloride solution - 1.0 ml.

One milliliter of a solution of a combination medication contains the following active substances:

Inosine glycyl-cysteinyl-disodium glutamate - 24.0 mg

Potassium chloride - 8.0 mg

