### **2. Dosage and Administration of the Combination Medication**

The combination medication is administered daily in the daytime 4 times a day with an interval of at least 4 hours.

The combination medication should be used within 24 hours after preparation.

A single inhalation dose of the combination medication is 1.25 ml.

A single dose of medication of the combination is as follows:

Inosine glycyl-cysteinyl-disodium glutamate – 30.0 mg

Potassium chloride – 10.0 mg

A daily dose of medication of the combination is as follows:

Inosine glycyl-cysteinyl-disodium glutamate – 120.0 mg

Potassium chloride – 40.0 mg

The combination medication is administered by inhalation using a nebulizer equipped with a mouthpiece. The nebulizer is connected to the compressor to create the required air flow (5-8 l/min). The combination medication should be inhaled through the mouthpiece of the nebulizer in a calm and regular manner.

The recommended duration of combined medicinal product use is 14 days.

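### Section 3 requires a nebulizer fill of at least 4 ml, which cannot be met together with its 1.25 ml single dose; the protocol does not show which rule needs correcting

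*Protocol*

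**What the plan says.** Protocol Section 3 (Dosage and Administration, as numbered in the body of the text) makes one preparation for the whole day: "The combination of the medication is prepared per daily inhalation dose by mixing the following medication in the indicated amount". The amounts are 4.0 ml of the 3% inosine compound solution and 1.0 ml of the 4% potassium chloride solution. The product is "administered daily in the daytime 4 (four) times a day with an interval of at least 4 hours", and "A single inhalation dose of the combination medication is 1.25 ml".

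The sentence on the nebulizer and its compressor then adds that "the nebulizer must be filled with at least 4 ml of the medicinal product". A little further on, the handling instructions say "Clean the cup of the nebulizer after each use".

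The instruction for use (Appendix 3) repeats the mix, the concentrations, the 1.25 ml dose and the frequency. It adds the amounts: 30 mg of the inosine compound and 10 mg of potassium chloride per inhalation, 120 mg and 40 mg per day. It also repeats the device sentence, "The nebulizer is connected to the compressor to create the required air flow (5-8 l/min", but ends it there, with no minimum fill.

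**The concern.** Section 3 gives whoever prepares an inhalation two rules, one for 1.25 ml and one for at least 4 ml of the same product, and does not say which prevails. Someone working from Appendix 3 alone never meets the second rule. The two texts can therefore lead to different amounts in the cup for the same prescription.

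The stake is consistent dosing over a 14-day course of 4 x 14 = 56 inhalations per volunteer. The objective covers both efficacy and safety. The product descriptions state for each component that there are no data on inhaled administration, so the protocol gives no basis for treating a larger load per inhalation as harmless. Safety findings can be tied to a single dose of 30 mg and 10 mg only if that dose is loaded in the same way each time.

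**Working it through.** **Inputs.** From Section 3 and Appendix 3: 4.0 ml of inosine compound solution and 1.0 ml of potassium chloride solution per day; four inhalations a day; 1.25 ml each. From the product descriptions: 30 mg/ml for the 3% solution and 40 mg/ml for the 4% solution. From Section 3 only: fill of at least 4 ml. Amounts below are given as inosine compound / potassium chloride.

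**The plan's own dose figures reproduce.**
- Mix volume: 4.0 + 1.0 = 5.0 ml.
- Concentrations: (4.0 x 30)/5.0 = 24 mg/ml and (1.0 x 40)/5.0 = 8 mg/ml, as stated.
- Single dose: 5.0/4 = 1.25 ml, holding 1.25 x 24 = 30 mg and 1.25 x 8 = 10 mg, as stated.
- Daily dose: 4 x 1.25 = 5.0 ml, or 120/40 mg, as stated.

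**The fill clause does not fit these figures.**
- One 4 ml fill: 4 x 24 = 96 mg and 4 x 8 = 32 mg loaded.
- Ratio to the single dose: 4/1.25 = 3.2.
- Share of the daily mix: 4/5.0 = 80%, leaving 1.0 ml for the other three inhalations.
- If the clause applies at every inhalation: 4 x 4 = 16 ml a day, and 16/5.0 = 3.2 times what is prepared.

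**Two ways to reconcile the rules, checked against the text.**
- *Load the day's mix once and inhale it in four parts.* The first fill of 5.0 ml would satisfy the clause, but 5.0 - 1.25 = 3.75 ml remains after one dose, which is already below 4 ml. The cup is to be cleaned after each use, and nothing says how to stop at 1.25 ml.
- *Top 1.25 ml up to 4 ml.* This would take 4 - 1.25 = 2.75 ml of diluent per inhalation, or 4 x 2.75 = 11.0 ml a day, and give 30/4 = 7.5 mg/ml and 10/4 = 2.5 mg/ml. Neither Section 3 nor Appendix 3 names a diluent, and the clause asks for 4 ml of the medicinal product itself.

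The text supports neither.

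**The case against.** The clause stands in the sentence on the compressor and air flow, so it can be read as an operating minimum of the device rather than as a dose. On that reading the 4 ml may be correct, the omission is a dilution step, and Appendix 3 is the incomplete text. This stands. A reader might infer from the agreement of all the other dose figures, and from the clause's absence in Appendix 3, that the clause is simply the error. The agreement shows only that the dose is settled. It says nothing about what the nebulizer needs, and the protocol names no model and gives no residual volume.

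The clause also does not say that it applies at each inhalation, so the 16 ml figure depends on that reading. This stands as well; the comparison of 4 ml with 1.25 ml does not depend on it.

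Finally, the consequence is bounded. The daily mix caps the day at 5.0 ml, the single dose is labelled as such in both places, and the instruction for use is free of the conflict. That limits the weight of the point. It does not remove the conflict, because Section 3 words the fill as a requirement and nothing elsewhere resolves it.

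**Conclusion.** The concern holds as an internal contradiction in Section 3 and should be fixed. A fill that meets the clause loads at least 3.2 times the stated single dose (96/32 mg against 30/10 mg). The shortfall of 16 ml against 5.0 ml follows only if the clause applies at every inhalation.

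The documents do not settle whether the clause is wrong or a dilution step is missing. A reader might go further and infer that volunteers would receive 3.2 times the intended dose. The documents do not support that either: the figure is an amount loaded, the delivered dose cannot be derived from the protocol, and the daily total stays at 120/40 mg as long as only the prescribed mix is made. The primary endpoint, sample size and analysis are not affected.

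**What to change.** Keep 1.25 ml of the mix (30/10 mg) as the single dose. Replace the requirement for at least 4 ml of the medicinal product with a loading rule, worded identically in Section 3 and in Appendix 3 and chosen according to the nebulizer used:

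- If the device is rated for 1.25 ml, load 1.25 ml undiluted.
- If the device needs 4 ml, load 1.25 ml of the mix plus 2.75 ml of a named diluent, inhaled in full.

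The first option costs a sentence in each place and a check of the device specification. The second is more than a wording change: it adds a component (11.0 ml a day) to the preparation steps in both places, lowers the inhaled concentration from 24/8 to 7.5/2.5 mg/ml and lengthens each inhalation. The choice depends on the device and belongs to the sponsor's clinical and pharmacy team.
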